## **13. ADVISORY COMMITTEES**

### **13.1 Steering Committee**

The Steering Committee (SC) will be composed of medical practitioners who are experts in the field of AF and LAA occlusion. The committee will serve as an advisory board during the course of the study as well as after its completion. Specific responsibilities of the members will depend upon the consulting expertise needed by the Sponsor. At any time during the course of the study, the SC may offer opinions or make formal recommendations concerning aspects of the study that impact subjects. Additionally, the SC may act as an advisory panel for questions that arise during the course of the study. It will be the responsibility of the SC to write a publication policy and along with SJM, review manuscripts and conference presentations.

### **13.2 Clinical Events Committee**

The clinical events committee (CEC) is an independent physician group that will review and adjudicate serious adverse events that occur over the course of the study. The CEC members will not be site investigators in the study. Responsibilities and membership of the CEC will be described in a CEC charter. Board membership may include cardiologists, electrophysiologists, neurologists and neuroradiologists.

The primary responsibilities of the CEC over the course of the study are to review and refine serious adverse event definitions, and to review and adjudicate serious adverse events.

### **13.3 Echocardiography Core Laboratory**

An independent echocardiography core laboratory (echo core lab) will analyze all TOEs, TTEs, and ICE images during the trial as required per the echo core lab protocol (**Appendix E**). The echo core lab will assess residual flow into the left atrial appendage around the device in the following manner:

- None – No color flow jet in or out of the LAA
- Small leak: < 3 mm diameter jet by color flow Doppler
- Medium leak: 3-5 mm diameter by color flow Doppler
- Large leak: > 5 mm diameter jet by color flow Doppler

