| Clinical Follow-up Visits/Testing | 
Subjects will be followed through two years post implant.
 
Required Testing
 
 
▪ Baseline evaluation: Informed consent, history and physical, pregnancy testing for women of childbearing age, 12-lead electrocardiogram (ECG), CHA2DS2-VASc score, HAS-BLED score, Modified Rankin Scale (mRS), medication assessment
 
▪ Procedure: Transoesophageal echocardiogram (TOE) or intracardiac echocardiogram (ICE) only when combined with baseline/pre-procedural TOE, angiogram, adverse event assessment
 
▪ Post procedure/Pre-Discharge: TTE, medication assessment, adverse event assessment
 
▪ 1M to 3M: TOE, medication assessment, adverse event assessment
 
▪ 6M (+/- 2 weeks): Phone contact follow-up for medication and AE assessment
 
▪ 12M (+/- 6 weeks): Medication and adverse event assessment
 
▪ 24M (+/- 12 weeks): Phone contact follow-up for medication and adverse event assessment
 
▪ Interim/unscheduled visits: per physician discretion
 
 |
| Suspected Stroke/TIA Evaluation   | 
 
▪ All subjects suspected of a stroke should be seen by a stroke/TIA neurologist for evaluation and appropriate neurological testing done (i.e. magnetic resonance imaging (MRI), computed tomography (CT))
 
▪ Modified Rankin Scale (Appendix J)
 
▪ TOE should be conducted to verify the presence of device-related thrombus
 
                                                                                                                                                                                                                                                                                                                                                                                                                                                                                                                                                                                                                                                                                                                                                    |

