ICE may be performed for placement of the device in a sub-set of centers pre-approved by SJM (see **Appendix K**)

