## **12. STATISTICAL METHODS**

No formal hypothesis will be tested for this observational post-market study. However, point estimates and exact 95% confidence intervals will be provided for the following rates in the study:

- Procedural serious adverse events (0 - 7 days) post procedure or before hospital discharge whichever latest) will be summarized for all subjects as well as stratified by imaging modality used for implanting the device (TOE and ICE)
- Late serious adverse events through 2 years
- Occurrence of ischemic stroke , systemic embolism and cardiovascular death through 2 years
- Occurrence of bleeding (including hemorrhagic stroke) events through 2 years

Data collected on the following objectives will also be reported:

- Technical success (secondary objective)
- Procedural success (secondary objective) - This objective will be summarized for all subjects as well as stratified by imaging modality used for placement of the device (TOE and ICE)
- OAC usage through 2 years (secondary objective)

- Serious Adverse Events – this may include, but is not limited to:
  - Significant bleeding events (e.g. cardiac tamponade, central nervous system (CNS) bleeding, and any bleeding related to the device or procedure that necessitates an operation)
  - Endocarditis
  - Device embolization (summarized by those that can be snared, and those that require surgical intervention)
  - Thrombus on device
  - All strokes
  - Transient ischemic attacks
  - Systemic embolism
  - Cardiovascular death
- Closure at procedure and 1-3 months post implant
  - The echo core lab's adjudication of residual flow will be used for this analysis. The following guidelines will be used:
    - None – No color flow jet in or out of the LAA
    - Small leak: < 3 mm diameter jet by color flow Doppler
    - Medium leak: 3-5 mm diameter by color flow Doppler
    - Large leak: > 5 mm diameter jet by color flow Doppler

Other variables may be summarized as deemed appropriate. The numerator for all rates will be the number of subjects who experience the corresponding event. The denominator for all rates will be subjects who experience the corresponding event plus all other subjects who achieve 2-years of follow-up.

Version 9.0 or higher of the SAS® statistical software package or other widely accepted statistical software will be used to provide all statistical analyses. Unless otherwise stated, attempts will not be made to adjust for multiple comparisons.

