## **Appendix E: Echocardiography Core Laboratory Protocols**

### **Transoesophageal Echocardiography (TEE) Protocol**

**ALL views to be provided in the following sequence:**

#### **I. TEE Scanning Protocol**

The following TEE protocol is recommended to ensure uniformity across clinical study sites. TEE studies are performed at baseline, during the procedure, at the 1-3 month and applicable follow-up/interim visits. The TEE study should image the left atrium (LA) and left atrial appendage (LAA) in multiple planes (i.e., 0°- ~110°). The purpose of the TEE is to obtain information regarding: a) LA/LAA thrombus; b) LAA ostium measurements; c) length distal to the LAA ostium; d) flow into the LAA and e) to assess for procedural complications, such as device migration, pericardial effusion, etc.

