#### **III. TEE Imaging Study to be Obtained in the Following Views:**

- a. The 5-chamber view (Omniplane 0°) with the aortic valve in the center of the screen and the LA in the right upper corner.
  - Standard 2D imaging.
  - Zoom mode of LA and LAA; place color flow Doppler (CFD) around device to document communication between LA and LAA (post procedure only).
  - Zoom mode of LA and LAA; align Pulse Wave (PW) Doppler sample volume to record LAA-LA blood flow. The PW sample should be placed 0.5 to 1 cm from the ostium into the LAA.

- 2D imaging of LV at mid-papillary muscle level (short axis), from gastric view.
- b. The high LA/LAA view (Omniplane ~60°)
- Optional views (these may be difficult to obtain in some subjects):
- Zoom mode of LA and LAA; place CFD around device to document communication between LA and LAA (post procedure only).
  - LA/LAA views; align PW Doppler sample volume to record LAA-LA blood flow. The PW sample should be placed 0.5 to 1 cm from the ostium into the LAA.
- c. The longitudinal imaging plane (Omniplane ~80-110°) with LA/LAA in field of view.
- Zoom mode of LA and LAA; place CFD around device to document communication between LA and LAA (post procedure only).
  - Zoom image of LA-LAA; align PW Doppler sample volume to record LAA blood flow. The PW sample should be placed 0.5 to 1 cm from the ostium into the LAA.

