## Appendix K: Intracardiac Echocardiography (ICE) Sub-Study Requirements

Requirements for intracardiac echocardiography (ICE) imaging include:

- Notification to SJM Clinical when ICE will be used for study implants:

| Contact                                              | Email                | Address                                                                                  | Telephone/Mobile/Fax                                                                    |
|------------------------------------------------------|----------------------|------------------------------------------------------------------------------------------|-----------------------------------------------------------------------------------------|
| [name]
Sr. Director Clinical Affairs | [contact]    | LAA Occlusion
St. Jude Medical
[name]
[name]
USA | Direct [name]
Main [name]
[contact]
[contact] |
| [name]
Clinical Programs Manager         | [contact] | LAA Occlusion
St. Jude Medical
[name]
[name]
USA | Direct [name]
Main [name]
[contact]
[contact] |

- Minimum of 5-10 ACP or Amulet cases using ICE performed by the study implanter/investigator
- Baseline TOE LAA measurements to assess the presence of thrombus and LAA anatomy
- Combined fluoroscopic and ICE guidance during the Amulet implant procedure to confirm device positioning and deployment
- Verification by ICE or fluoroscopy to confirm device stability

|  |                                                                                                                 |
|--|-----------------------------------------------------------------------------------------------------------------|
|  | Study Document No: SJM-CIP-10053 Version A
Study Name: AMPLATZER™ Amulet™ Observational
Post-Market Study |
|  |                                                                                                                 |

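### Procedural closure has no specified image acquisition when the implant is guided by ICE alone, and the denominator for rates does not require a readable study

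*Protocol*

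**What the plan says.** Section 12 lists "Closure at procedure and 1-3 months post implant" among the additional data to be reported, and fixes the source: "The echo core lab's adjudication of residual flow will be used for this analysis". Section 13.3 says the core laboratory "will analyze all TOEs, TTEs, and ICE images during the trial as required per the echo core lab protocol", with a pointer to Appendix E. Sections 12 and 13.3 both grade leaks by jet diameter on colour Doppler (none, under 3 mm, 3-5 mm, over 5 mm) without naming a modality.

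On which imaging is done at the implant, the protocol gives three accounts:

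- The synopsis (Required Testing) asks for TOE, or "intracardiac echocardiogram (ICE) only when combined with baseline/pre-procedural TOE".
- Table 2 marks TOE at the procedure. A footnote adds that "ICE may be performed for placement of the device in a sub-set of centers pre-approved by SJM".
- Appendix E, part I, states that "TEE studies are performed at baseline, during the procedure, at the 1-3 month and applicable follow-up/interim visits".

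Appendix K sets the ICE requirements: notification of the sponsor, prior operator experience, a baseline TOE, combined fluoroscopic and ICE guidance, and "Verification by ICE or fluoroscopy to confirm device stability".

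Section 12 also sets one rule for all rates. The numerator is the subjects with the event. The denominator is those subjects plus everyone else who completes two years of follow-up.

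**The concern.** An outcome read by a core laboratory depends on the images that sites are told to record. For TOE implants the protocol gives that instruction. For ICE implants the reference from Section 13.3 leads to an appendix that never mentions ICE, and the ICE appendix deals with placement and stability, not residual flow.

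A site following the synopsis could complete an ICE implant correctly and send the laboratory nothing on which a leak can be graded. Loops that were never recorded cannot be recovered later by any analysis plan. The denominator rule would still count those subjects if they reach two years, so a missing reading would enter the rate as if it were a result.

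**Working it through.** The protocol states no closure rate, ICE share, power or margin, so there is no figure to reproduce. The check is a comparison of passages, followed by an illustration on assumed inputs.

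**Does any passage require a gradable post-release image in an ICE implant?**

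1. *Appendix E, TEE part.* The relevant instruction is "place color flow Doppler (CFD) around device to document communication between LA and LAA (post procedure only". It appears only under views defined by TEE probe angle. The flow grading in part VII belongs to the same TEE protocol.
2. *Appendix E, TTE part.* It covers the left ventricle, the valves, the atrial septum and complications such as effusion. It asks for no colour flow at the appendage or around the device, so the pre-discharge TTE does not fill the gap.
3. *Appendix K.* The baseline TOE precedes the device. ICE then serves positioning and deployment, and fluoroscopy may replace it for the stability check. No colour-flow recording is listed.
4. *Table 2 and Appendix E, part I.* Read literally, a TOE is done at the procedure in everyone, which would supply the reading. The synopsis allows ICE instead. Neither side says how the other applies to ICE cases, so sites could follow different rules.

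**What does the denominator rule do with unread subjects?**

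Assumptions, none from the protocol: 1000 implants (the planned size), all followed for two years; a true leak rate p = 10% regardless of modality; an ICE share f of 2% to 30%.

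- Unread ICE subjects kept in the denominator, leak as the event: reported leak = (1 − f) × p.
- The same, with closure as the event: reported closure = (1 − f) × (1 − p).
- ICE images graded but showing half the leaks: reported leak = (1 − f) × p + f × p/2.

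| ICE share f | ICE subjects | Leak, ICE unread | Closure, ICE unread | Leak, ICE shows half |
|---|---|---|---|---|
| 2% | 20 | 0.98 × 10% = 9.8% | 0.98 × 90% = 88.2% | 9.8% + 0.1% = 9.9% |
| 10% | 100 | 0.90 × 10% = 9.0% | 0.90 × 90% = 81.0% | 9.0% + 0.5% = 9.5% |
| 20% | 200 | 0.80 × 10% = 8.0% | 0.80 × 90% = 72.0% | 8.0% + 1.0% = 9.0% |
| 30% | 300 | 0.70 × 10% = 7.0% | 0.70 × 90% = 63.0% | 7.0% + 1.5% = 8.5% |

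The exact 95% interval for 100 leaks in 1000 is 8.2% to 12.0%. With unread subjects counted, the leak rate stays inside that interval at a 10% share and falls just below it at 20%. With half the leaks seen, it stays inside throughout.

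The denominator rule also makes the result depend on which outcome is called the event. At a 30% share, leak is 7.0% and closure 63.0%; they sum to 70%, and the missing 30% is the unread group. With readable studies only, the expected leak rate stays at 10% under these assumptions, and the cost is precision: for 70 of 700 the interval is 7.9% to 12.5%.

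**The case against.** The strongest reply is that the protocol does call for a procedural TOE. Table 2 and Appendix E say so without exempting ICE cases, and the synopsis lists TOE with colour flow among the clinical procedures. A reader might infer that closure is simply unmeasured in the ICE group; the documents do not establish that. Nor does Section 13.3 promise a reading for every implant, since it covers images as Appendix E requires them. What stands is that the synopsis can be read the other way and the text does not settle which applies.

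A reader might also infer that the leak grades were written only for TOE. They were not: Sections 12 and 13.3 give them without a modality, so an ICE loop with usable colour flow could be graded. Appendix K's list is introduced as what the requirements include, so it is not stated to be exhaustive, and the instructions for use are not at hand. These points leave the grading in place but do not supply an acquisition instruction.

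It is also tempting to say that ICE subjects will show a false change in leak between the procedure and 1-3 months. Section 12 reports closure at two time points and plans no paired or change analysis, so that harm is not in the plan.

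Finally, a table of closure by modality, or a closure-specific denominator, could properly sit in a statistical analysis plan that is not shown. The missing split is therefore no fault by itself, and it does not show that closure will only be pooled. An analysis plan cannot, however, create images that were not recorded, and the denominator in Section 12 is stated for all rates.

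**Conclusion.** The point holds in a limited form. For implants guided by ICE alone, the protocol specifies no acquisition for procedural residual flow, so that reading may be missing or not comparable with TOE. The passages on procedural TOE disagree, and the denominator rule does not require a readable study.

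The consequence is small for the study as a whole. Closure is neither a primary nor a secondary objective, no hypothesis is tested, ICE is restricted to pre-approved centres, and the 1-3 month reading uses TOE whatever the implant modality. In the illustration, the pooled leak rate moves by 0.2 points at a 2% ICE share and 3.0 points at 30% if ICE subjects are unread but counted, and by 0.1 to 1.5 points if ICE shows half the leaks. These sizes rest on an assumed 10% leak rate and assumed ICE shares. The figure that would be unreliable is procedural closure in the ICE subjects themselves.

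**What to change.** 1. Reconcile the synopsis with Table 2 and Appendix E, part I, on whether ICE cases also have a procedural TOE, and state the answer once.
2. Add an ICE section to Appendix E, with a matching line in Appendix K, asking for colour-flow Doppler loops around the device after release, graded on the existing Section 13.3 scale.
3. In Section 12, exempt procedural closure from the general denominator and use subjects with a readable study. Show the number assessed and the result for TOE and ICE separately, as Section 12 already does for procedural serious adverse events and procedural success.

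The cost is a short addition to two appendices, a few more recorded loops in an ICE study already under way, and one more table. A readable-study denominator gives a somewhat wider interval where readings are missing, and it assumes that unread subjects resemble those who were read; the counts by modality let a reader judge that. Item 2 needs to be in force before ICE implants are done, because the images cannot be obtained afterwards.

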## **14. DOCUMENT RETENTION**

After the termination of the study, the principal investigator will maintain all clinical study documents on file at the site for the minimum number of years required per local laws.

## **15. AMENDMENTS TO THE CLINICAL PROTOCOL**

Study related documents such as, the Investigator's Brochure (IB) (**Appendix D**), protocol, eCRFs (**Appendix H**) informed consent form (**Appendix G**) and other subject information, or other clinical study documents will be amended as needed throughout the clinical study, and a justification statement will be included with each amended section of a document. Proposed amendments to the protocol will be agreed upon between the Sponsor and the coordinating investigator (if applicable).

The amendments to the protocol and the subject's informed consent form will be notified to, or approved by, the EC and regulatory authorities, if required. The version number and date of amendments will be documented (**Appendix B**).

The amendment will identify the changes made, the reason for the changes and if it is mandatory or optional to implement the amendment. Any amendment affecting the subject requires that the subject be informed of the changes, and a new consent be signed and dated at the subject's next follow up.

## **16. OUTSOURCING OF SPONSOR DUTIES AND FUNCTIONS**

The Sponsor does not anticipate transferring any duties and functions related to the clinical study, including monitoring, to an external organization (such as a contract research organization or individual contractor). If outsourcing does occur, the ultimate responsibility for the quality and integrity of the clinical study will reside with the Sponsor. All requirements applying to the Sponsor will also apply to

the external organization inasmuch as this organization assumes the clinical study related duties and functions of the Sponsor.

## **17. INVESTIGATION SUSPENSION OR TERMINATION**

### **17.1 Premature Termination**

The Sponsor reserves the right to stop the study at any stage, with appropriate written notice to the investigator.

Possible reasons for early termination of the study by the Sponsor, either at local, national or international level, may include, but are not limited to:

- Sponsor's decision
- Request from regulatory authorities
- Request of EC(s)
- Concern for subject safety and welfare
- Failure to secure subject informed consent prior to any protocol activity
- Failure to report unanticipated adverse device effects within 72 hours to SJM and the EC
- Repeated non-compliance with this clinical protocol or the clinical trial agreement
- Inability to successfully implement this clinical protocol
- Violation of the Declaration of Helsinki (refer to Appendix C)
- Violation of applicable national or local laws and regulations
- Falsification of data, or any other breach of ethics or scientific principles

In such events, the study will be terminated according to applicable regulations. The investigator may also discontinue participation in the clinical study with appropriate written notice to the Sponsor. Should either of these events occur, the investigator should provide a written statement as to why the premature termination has taken place, and notify the EC and/or the CA (if applicable). Follow-up for all enrolled subjects will be per center standard of care.

A principal investigator, EC, or regulatory authority may suspend or prematurely terminate participation in a clinical study at the investigational sites for which they are responsible.

### **17.2 Study Conclusion**

The study will be concluded when:

- All follow up visits have been completed and subjects withdrawn AND
- All sites are closed AND
- The final report generated by SJM has been provided to sites or SJM has provided formal documentation of study closure

## 18. PUBLICATION POLICY

The results of the clinical study are planned to be submitted for publication. If a principal investigator will be involved in publishing the data, a publication agreement will be signed between the PI and Sponsor either as a separate publication agreement or within the clinical trial agreement.

The investigator or site may not publish any information that the Sponsor believes to be confidential information. The publication of the initial results of the Amulet observational post-market study shall be subject to review and release of the Sponsor's publication committee, which shall confer with the site regarding such publication.

For more information on publication guidelines, refer to the International Committee of Medical Journal Editors (ICMJE) on [www.icmje.org](http://www.icmje.org). This study will also be posted on ClinicalTrials.gov and results will be posted on ClinicalTrials.gov as required.

